**For all participants enrolled in Stratum A (mild disease) or Stratum B (cirrhosis) inclusion criteria are**

1. Aged ≥ 18 years
2. At least one detectable viraemia prior to the screening visit (by quantitative HCV RNA, qualitative assay or HCV genotype), with no intervening undetectable results
3. Plasma HCV RNA >LLOQ at screening
4. BMI >=18kg/m^2^
5. Laboratory tests: creatinine clearance (estimated using Cockcroft-Gault) >=60ml/min, international normalised ratio (INR) <1.5xULN
6. Written informed consent obtained from the patient.

**For Stratum A, additional inclusion criteria are**

1. Infected with HCV genotype 1 (all subtypes) or genotype 6 (all subtypes)
2. Mild liver disease: No evidence of significant liver fibrosis resulting from any aetiology, defined as

EITHER
(a) Fibroscan* score ≤7.1kPa, equivalent to F0-F1 [[19](#_ENREF_19)], within 180 days prior to planned enrolment,

OR
(b) biopsy consistent with mild fibrosis (Ishak score <=2/6) within 180 days prior to planned enrolment

**For Stratum B, additional inclusion criteria are**

1. Infected with HCV genotype 6 (all subtypes)
2. Compensated Cirrhosis: Evidence of compensated cirrhosis resulting from any aetiology defined as

EITHER
(a) Fibroscan* score ≥10.1kPa within 180 days prior to enrolment

OR
(b) biopsy consistent with cirrhosis (Ishak score >=5/6 or equivalent) within 180 days prior to enrolment)

OR
(c) Imaging (Ultrasound or CT or MRI) reported as showing cirrhosis

1. Childs-Pugh Score ≤7 according to following scoring system

* Fibroscan must be a valid result (based on at least 10 readings) performed by an experienced (as evidenced by CV and/or training logs) technician.

- 1. Exclusion Criteria

1. Previous Hepatitis C (treatment with DAAs, and/or pegylated-interferon and/or ribavirin)
2. HIV infected
3. Solid Organ Malignancy within 5 years prior to screening
4. Any condition in the judgement of the investigator which might limit the patient’s life expectancy within the duration of the study
5. Any disorder or circumstance which in the opinion of the investigator may have a significant negative impact on the ability of the patient to adhere to the trial regimen
6. HBsAg positive
7. Disorder which may cause ongoing liver disease including, but not limited to, ongoing alcohol misuse
8. Currently receiving medication known to interact with study medications for which dose adjustment for daclatasvir or sofosbuvir would be recommended in the Summary of Product Characteristics
9. Use of other investigational products in clinical studies within 60 days of screening
10. History of severe pre-existing cardiac disease, including unstable or uncontrolled cardiac disease, in the previous six months
11. Patients currently using amiodarone or other anti-arrhythmics (including patients with permanent pacemakers).
12. Pregnancy
13. Symptomatic Haemoglobinopathy (e.g., thalassemia major, sickle-cell anaemia).
14. Unlikely to be able to attend follow-up visits for any reason, as judged by the attending physician
    1. Number of Participants

In total, 103 participants will be recruited, stratified by stage of liver disease. 60 participants will be recrutied with mild liver disease (30 genotype 1, 30 genotype 6). 43 participants will be recruited with compensated cirrhosis (genotype 6 only)

1. REGISTRATION AND RECRUITMENT
   1. Recruitment and retention strategies

Participants will be recruited in Ho Chi Minh City, Vietnam at the Hospital for Tropical Diseases. Potential participants will be identified and approached by clinic staff to participate in the trial. In addition, appropriate patients who are part of the Hepatitis Cohort will be approached for participation in line with previous permissions. Recruitment activities will only occur in an out-patient hospital setting and no activities will be carried out outside of the participating hospital. The target sample size of 103 participants will be enrolled.

To ensure an optimal retention rate, participants will be contacted by phone to remind them of their next visit. In addition, participants who have missed a visit will be contacted by phone for a maximum of three times after which a maximum of three home visits can be conducted.

- 1. Screening Procedures & Pre-enrolment Investigations

All potential participants will be identified for screening in the out-patient department of the HTD, HCMC. As part of their standard care participants will have routine laboratory tests, including liver function tests; hepatitis C viral load and genotyping; HIV tests, and Fibroscan. These tests will be used to identify participants who may be suitable for screening.

The name and date of birth of every adult screened for the trial will be added to the site Screening & Enrolment Register, together with allocated trial number if subsequently enrolled, or the reason the participant was not enrolled. The Screening & Enrolment Register will be kept in a secure location and will be the responsibility of the site Principal Investigator.

A fibroscan or biopsy result will be valid if conducted within the 180 days preceding enrolment. The screening visit may be conducted up to 60 days prior to recruitment, providing that results of blood tests to confirm eligibility in terms of laboratory abnormalities and HCV VL are available.

- 1. informed consent

The site PI or an appropriately trained doctor must seek written informed consent from patients to enter into the trial in their own language. Individuals trained and responsible for taking consent will be documented on the trial’s Delegation Log (with signatures). Consent will be sought after explanation of the aims, methods, benefits and potential hazards of the trial and BEFORE any trial-specific procedures are performed or any blood is taken for the trial, including for the screening assessment.

The doctor taking consent must make it completely and unambiguously clear that the participant is free to refuse to participate in or withdraw from all or any aspects of the trial, at any time and for any reason, without incurring any penalty or affecting their subsequent treatment. This will be stated explicitly in the participant information sheet.

Signed consent forms must be kept by the investigator and documented in the case record form (CRF) and a copy given to the participant.

- 1. Co-enrolment Guidelines

Treatment with any other investigational product within 60 days prior to screening is an exclusion criteria, and therefore co-enrolment with a previous investigational medicinal product (IMP) trial will generally not be allowed, unless the patient is in a follow-up phase. Before enrolment into the study of a patient already participating in a previous trial (not of an investigational product), the site investigator must confirm with the investigators of the previous trial that co-enrolment is allowed. Co-enrolment in the study of patients already participating in an observational study is allowed.

1. TReatment of PARTICIPANTS

Each participant will be treated with the same drug combination (sofosbuvir 400mg and daclatasvir 60mg daily), but with differing durations of therapy. The study design is open-label; bias will be minimised by using objective laboratory measurements to determine duration of therapy and to assess treatment outcomes .

Any patient in the mild disease cohort who experiences failure of first-line treatment will initiate re-treatment as soon as possible after failure is identified. Failure of first-line treatment during the study is defined as

1. two consecutive measurements of HCV RNA > LLOQ (taken at least one week apart) after two consecutive visits with HCV RNA <LLOQ, at any time during the study follow-up period, with the latter confirmatory measurement also being >2000 IU/ml OR
2. two consecutive measurements of HCV RNA (taken at least one week apart) that are >1 log10 above the nadir on treatment and >2000 IU/ml, at any time during the study follow-up period.

Failure as defined forms part of the definition of the primary endpoint, see section 2.2.

Patients will have ultrasound and AFP monitoring in line with Vietnamese national guidelines; that is at study entry, end of treatment and 12 weeks after the end of treatment. Study follow-up completes at 12 weeks after the end of treatment, or re-treatment, for all patients. Following study participation, all patients will return to normal standard of care follow-up within the hospital where they will undergo follow-up for up to 2 more years according to national guidelines.

- 1. Treatment Schedule

The duration of first-line SOF/DCV treatment will be determined by the initial response to treatment, as outlined in trial schema above

**STRATUM A (mild liver disease, G1 and 6 HCV, Ultrarapid Repsonse Guided Therapy)**

All participants will receive a minimum of 4 weeks of therapy. All indiviudals will have HCV viral load assayed at enrolment and 24 and 48 hours after initiation of therapy (first dose to be taken in the clinic at D0). For participants with viral load <500IU/ml (as measured by Cobas assay, Roche) at 48 hours (Day 2 visit), treatment will be completed at 4 weeks. All other participants will receive 8 weeks of therapy. Following cessation of first line therapy (at the end of treatment (EOT) visit), all participants will have HCV viral load assayed twice weekly for four weeks so that the kinetics of any viral rebound post-EOT can be captured in detail. Participants meeting the definitions of first line failure above will be eligible for retreatment according to protocol at any time after EOT +2 weeks.

**STRATUM B (compensated cirrhosis, G6 HCV only, Response guided therapy)**

All participants will receive a minimum of 12 weeks of treatment. Those participants who have achieved virological suppression (VL <500IU/ml, as measured by Cobas assay, Roche) at the time of their D14 visit or sooner after treatment initiation will complete therapy at 12 weeks. Those who do not achieve virological suppression will continue to complete 24 weeks of therapy.

- 1. Protocol Treatment Discontinuation

In consenting to the trial, participants are consenting to trial treatment, trial follow-up and data collection.

Treatment (or retreatment) will be discontinued if any of the following occurs:

- toxicity which the investigator considers impedes the ability of the patient to continue intervention and/or the product information for the drug(s) contains a directive on discontinuation in the event of this specific toxicity
- participant requests for any reason to withdraw consent for treatment
- virological failure as defined above (move to retreatment if first-line failure and mild disease)

However, any such patient discontinuing study treatment (or retreatment) will be invited to continue follow-up “off study drug, on study” in order to obtain data on overall cure and adverse events. Participants should only discontinue study follow-up if they explicitly withdraw consent to continue to attend study visits. In this situation, participants may still contribute data collected at their routine clinic visits to the trial, providing they are willing to do so (“off study, follow-up through medical records only”).

1. Assessments & Follow-up
   1. Trial Assessment Schedule

See Appendix II, Trial Assessment Schedule.

All participants will be followed by the site clinic teams for 12 weeks after the end of first-line treatment or re-treatment (where relevant) for evaluation of virological response and toxicity. Outcome measures will be assessed at clinic visits (see Trial Assessment Schedule). For the mild disease cohort, the first DAA dose should be taken in the clinic and the blood draws on day 1 and day 2 should be taken within ±3 hours of 24 and 48 hours post this first dose wherever possible. Other on treatment visits should occur within ±1 days wherever possible, and the post end-of-treatment (EOT) visits within ±3 days. However, if this is not possible, a visit (with all the appropriate tests and evaluations) should still take place outside this window to ensure that trial outcomes are ascertained as accurately as possible in real-time.

All those recording clinical data will be identified and receive appropriate training and sign the Delegation Log. Clinical data will be obtained through consultation with the participant, their medical team, or their medical records. Laboratory measures and resource utilisation will be extracted from participant notes/electronic records; study nurses will administer quality of life questionnaires to participants.

Any additional visits or diagnostic/laboratory tests needed for patient management should occur as required at the discretion of the treating physician. Results from these investigations should be recorded on CRFs, but only the investigations specified in the Trial Assessment schedule are required in all participants.

- 1. Procedures for Assessing Efficacy

The primary means of assessing efficacy is the HCV viral load. HCV viral load will be assayed locally in line with existing clincial practice. This will also enable swift detection of virological failure and move to re-treatment for participants in the mild disease cohort.

HCV viral resistance will be measured within the SEARCH consortium retrospectively in batches during the trial. This will be done using next-generation sequencing approaches. Viral genotype will also be characterised using these assays enabling an assessment of whether treatment failure is a genuine recurrence (same genotype, closely genetically related) or a new infection (different genotype, or same genotype but genetically too distant to be compatible with within-host evolution). Summary resistance data will be shared with the local research team.

In terms of incidental findings from these next generation sequencing studies, we will follow the principles that health related findings (HRFs) identified during viral genetics studies that are associated with serious and treatable infectious disease WILL be fed back to participants. The only pathogens falling within this category of HRFs at the current time are HIV and Hepatitis. HRFs identified during host genetics studies will NOT be fed back to participants.

- 1. Procedures for Assessing Safety

Laboratory assessments to ensure patient safety will be performed routinely, and additional safety blood tests or investigations may be performed to investigate symptoms or monitor emergent laboratory test abnormalities as clinically indicated. Laboratory abnormalities that require medical or surgical intervention or lead to an interruption, modification, or discontinuation in study medication will be recorded as an AE, as well as an SAE (if applicable).

Clinical AEs and SAEs will be elicited (together with relationship to study medications) throughout the study at the regular clinical assessments, through consultation with the participant, their medical team, or their medical records.

In addition, laboratory or other abnormal assessments (eg, electrocardiogram, x-rays, vital signs) that are associated with signs and/or symptoms must be recorded as an AE or SAE if they meet the definition of an AE or SAE (see Section 8). If the laboratory abnormality is part of a syndrome, the diagnosis or syndrome will be recorded (eg, anaemia), in preference to the laboratory result. The severity grading of AEs will be assessed as Grade 1, 2, 3, or 4 using the Common Toxicity Criteria grading scale (see Appendix III).

All AEs should be recorded in the patient’s source documents, only those which are:

- serious,
- reactions (any grade) considered definitely/probably/possibly related to SOF or DCV,
- clinical grade 3 or 4,
- any grade leading to change in treatment (SOF, DCV or any other medication)

need to be reported on trial CRFs.

See Safety Reporting Section 8 and Section 8.2 in particular for investigator’s responsibilities regarding assessment of seriousness, causality and expectedness, and reporting to OUCRU CTU.

Any participant experiencing an AE or SAE will be followed up until resolution or stabilisation of the AE. For AE/SAEs leading to discontinuation of study medication, patients will continue to be followed up “off study drug, on study”. Any participant who wishes to withdraw from study visits after an AE/SAE leading to discontinuation of study medication must still be followed up in routine clinics for 12 weeks following cessation of therapy.

- 1. Other assessments

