**Viral hepatitis in Vietnam**

Vietnam (gross per capita income $1980 in 2015) has an estimated 31,000 deaths from viral hepatitis each year, the 9^th^ highest amongst all countries. In a population of 90 million, an estimated 1.07 million are infected with HCV [[2](#_ENREF_2)]. The HCV epidemic in Vietnam poses particular challenges under-served by current research in the field. The majority of HCV patients are infected with genotype 6 (G6) virus (approx. 54%), a genotype that is relatively uncommon beyond Vietnam’s immediate neighbours (Laos, Thailand and South China) but which accounts for over 5% of the 180 million infected individuals globally [[3](#_ENREF_3)]. HCV G6 has evolved in S.E Asia over >1000 years, in spatially restricted local epidemics, generating enormous viral genetic diversity [[4](#_ENREF_4)]. Despite large Phase III programmes for new HCV treatments, very few G6 patients have been included in these studies (the largest cohort to date is 49 patients) and the evidence base for treatment is small. In addition, the burden of HCV/HIV co-infection is high in Vietnam with an estimated 44,000 HIV/HCV co-infected individuals.

[figure not shown]

Figure 1 Proportion of HCV infected patients with genotype 6 by country

Treatment of HCV is available in Vietnam, but access even to interferon-based therapy is still relatively limited. The Government currently provides interferon-based therapy and those who have insurance co-pay at least 30% of its cost. Very few patients have access to novel oral treatments, which are only available privately. Although costs will continue to fall with increasing access to generic drugs, treatment will still be prohibitively expensive for most infected individuals. Therefore, any type of treatment will remain beyond the reach of most for the near future.

The work proposed here has its emphasis on infection with HCV genotype 6 (G6), the dominant genotype in Vietnam. This genotype is dominant across Southeast Asia but substantially underrepresented in trials to date

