**Risks and benefits at patient and societal level**

The primary benefit of participation for individual patients in this trial is that >90% of individuals will achieve cure of hepatitis C without interferon-based treatment within the protocol. For many, interferon will have been a barrier to accessing and/or adhering to treatment previously. Barriers to accessing treatment are likely to remain even with increasing availability of directly acting antivirals (DAAs), as demand for treatment is expected to exceed the capacity to deliver it in setting such as Vietnam. The primary outcome measure (sustained virological response 12 weeks after end of treatment, SVR12) has been associated with significant reductions in all-cause mortality, cirrhosis and liver cancer [[18](#_ENREF_18)], and so achieving cure will significantly reduce individual patient’s future risks of these events. The study will use licensed medications that have been recommended as part of the WHO Essential Medicines list since 2015.

1. trial design and endpoints
   1. Description of trial design

The study is a single arm, open label trial with the objective of identifying successful strategies for shortening treatment for individuals chronically infected with hepatitis C based on their early response to therapy.

It will test the hypothesis that early responses to treatment with sofosbuvir and daclatasvir will identify a group of individuals able to achieve high cure rates with shortened courses of treatment. Participants will be stratified by stage of liver disease to one of two strategies based on virological response after either 48 hours (non-cirrhotic) or 14 days (cirrhosis) of starting treatment.

- 1. trial endpoints

Primary endpoint

The primary endpoint for the trial is Sustained Virological Response (SVR12) defined as plasma HCV RNA <LLOQ (lower limit of quantification, <15 IU/ml) 12 weeks after the end of first treatment without prior failure defined as either:

i. two consecutive measurements of HCV RNA >LLOQ (taken at least one week apart) after two consecutive visits with HCV RNA <LLOQ, at any time, with the latter confirmatory measurement also being >2000 IU/ml

ii. two consecutive measurements of HCV RNA (taken at least one week apart) that are >1 log10 increase above HCV RNA nadir on treatment and >2000 IU/ml, at any time.

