For both treatment strata, the target cure rate is 90%, with an unacceptably low cure rate of 70% (final lower 95% CI limit should exceed this). Assuming 90% power and one-sided alpha=0.05, requires 37 participants to exclude the null hypothesis (cure <90%). Assuming 5% loss to follow-up in both strata, and that 65% (based on [[12](#_ENREF_12)]) and 90% achieve on-treatment response and receive shortened therapy in Stratum A and B respectively, 60 participants would be required in Stratum A (pooling genotypes), and 43 in Stratum B. 5% loss follow-up is consistent with experience in the local setting which has generally followed patients for much longer than 12 weeks post end of treatment as here [personal communication, OUCRU].

- 1. Analysis Plan (Brief)

The analyses will be described in detail in a full Statistical Analysis Plan. This section summarises the main issues.

The primary analysis would be intention-to-treat, including all participants regardless of treatment received. Primary analysis of SVR12 (the primary endpoint) would be as observed (those not meeting the formal “failure” definition but discontinuing first-line treatment early and not undergoing re-treatment with detectable HCV RNA 12 weeks later counted as not achieving the primary endpoint). Any missing data at 12 weeks post EOT due to assay failure or missed visit would be multiply imputed within stratum based on all viral load measurements and baseline characteristics, using chained estimating equations. Continuous variables would be transformed for normality, and data augmented following standard recommendations to avoid problems with perfect prediction. The distribution of imputed data would be checked versus observed data.

Secondary analyses for each outcome would be based on a per-protocol population, which we (arbitrarily) define as receiving >90% and <110% of the prescribed duration of first-line treatment. Assessment of treatment received will be based on both prescription and self-reported adherence.

A further secondary analysis will exclude reinfections leading to rebound virus, with reinfection determined by genotype and full genome sequencing.

As the duration of follow-up is relatively short, primary analysis would consider outcomes as binary. Proportions and their 95% CI would be estimated using Poisson regression.

1. Data management
   1. source data

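### The reinfection rule used in one secondary analysis does not check whether the rebound strain was already present at day 0, so a surviving minor strain would be excluded as a new infection

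*Protocol*

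**What the plan says.** Section 6.2 (Procedures for Assessing Efficacy) plans viral sequencing during the trial: "This will be done using next-generation sequencing approaches". The results are to show, in its words, "whether treatment failure is a genuine recurrence (same genotype, closely genetically related". The other class named there is "a new infection (different genotype, or same genotype but genetically too distant to be compatible with within-host evolution". These are the only two classes given. Neither refers to the mix of strains at entry.

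Section 9.2 (Analysis Plan) then uses the label: "A further secondary analysis will exclude reinfections leading to rebound virus, with reinfection determined by genotype and full genome sequencing". This is the only analysis in which the protocol uses it.

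The primary analysis is separate from this: "The primary analysis would be intention-to-treat, including all participants regardless of treatment received". The primary endpoint in Section 2.2 requires HCV RNA below the quantification limit "12 weeks after the end of first treatment without prior failure defined as either" of two viral-load criteria. It makes no exception for reinfection.

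On entry, Stratum A takes participants "Infected with HCV genotype 1 (all subtypes) or genotype 6 (all subtypes"), and Stratum B takes genotype 6 of any subtype. Sections 3.1 and 3.2 do not mention infection with more than one strain.

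**The concern.** The rule infers the origin of a rebound only from how far the rebound virus lies from the treated virus. Two different histories look the same on that measure:

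- **Reinfection.** The participant cleared the treated virus and later acquired another.
- **Mixed infection at entry.** The participant carried two genotypes or subtypes, treatment cleared the dominant one, and the minor one survived and grew back.

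The second is a failure of the course being tested. Under Section 6.2 it would be called a new infection, and under Section 9.2 it would be left out. Only rebounds can carry the label, so each failure misread in this way removes a failure and no cure. The analysis is meant to give a cure rate free of reinfection, and with about 37 participants on shortened therapy per stratum a single case is visible in the result.

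**Working it through.** **Inputs.** From Section 9.1: target cure 90%, unacceptable cure 70%, one-sided alpha 0.05, power 90%, 37 participants on shortened therapy, 5% loss, 65% (Stratum A) and 90% (Stratum B) receiving shortened therapy, stratum sizes 60 and 43. Assumed: k, the number of surviving minor strains misread as reinfection, is 0 to 2 per stratum. Also assumed: exclude means that the participant leaves the denominator, which the protocol does not state.

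**Step 1. The plan's own figures.** An exact one-sample binomial test with null 70% and alternative 90% at n = 37 requires at least 31 cures, with one-sided alpha 0.044 and power 0.929, so 37 is reproduced. Inflation gives 37/(0.65 × 0.95) = 59.9, stated as 60, and 37/(0.90 × 0.95) = 43.3, stated as 43. I therefore use n = 37 as the reference size. The point does not touch these figures.

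**Step 2. Effect of a misread failure.** With x cures among n participants, excluding k failures changes the estimate from x/n to x/(n − k), a gain of x·k/[n(n − k)].

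| Cures x of n | k = 0 | k = 1 | k = 2 |
|---|---|---|---|
| 31 of 37 | 83.8% | 31/36 = 86.1% (+2.3) | 31/35 = 88.6% (+4.8) |
| 33 of 37 | 89.2% | 33/36 = 91.7% (+2.5) | 33/35 = 94.3% (+5.1) |

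For example, 33 × 1/(37 × 36) = 0.0248, or 2.5 points.

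**Step 3. Whole stratum as denominator.** After 5% loss, 60 × 0.95 = 57 and 43 × 0.95 ≈ 41 remain. One exclusion moves 51/57 = 89.5% to 51/56 = 91.1% (+1.6), and 37/41 = 90.2% to 37/40 = 92.5% (+2.3).

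**Step 4. Primary SVR12.** The endpoint in Section 2.2 and the failure criteria there and in Section 5 use viral load only. A rebound that meets them counts as failure whatever its sequence. The change is 0 points at every k.

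**Step 5. Could one case carry the result across 70%?** Lower limits at 31/37 and, after one exclusion, 31/36:

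| Method | 31/37 | 31/36 |
|---|---|---|
| Exact, two-sided 95% | 68.0% | 70.5% |
| Exact, one-sided 95% | 70.5% | 73.0% |
| Poisson, robust standard error | 72.7% | 75.5% |
| Poisson, model-based standard error | 58.9% | 60.6% |

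Only the first row crosses 70%.

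**The case against.** The strongest reply is that the protocol leaves this open. Section 9.2 is a summary that defers detail to a full statistical analysis plan, and read thresholds or the handling of failed sequences commonly belong there. The wording in Section 6.2 may describe what sequencing makes possible and not a closed algorithm, and the planned methods could detect minor strains at entry. This stands for the laboratory detail. It does not stand for the two classes, which the protocol states itself: an analysis plan that follows them faithfully would put a surviving minor strain in the wrong one.

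It can also be said that nothing in the document shows mixed infection to be common here. That is correct. The background describes genotype 6 as evolving in local epidemics, "generating enormous viral genetic diversity", but this concerns diversity across the population and is no evidence of mixed infection within a patient. The frequency remains an assumption.

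Four stronger readings are tempting, and the document does not support them:

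- **That the trial's main cure rate is overstated.** The label enters one secondary analysis only, and the primary SVR12 does not use it.
- **That every misclassification favours the trial.** A true reinfection with a closely related strain would be called a recurrence and kept as a failure, which lowers the estimate.
- **That one case can turn a failed result into a success.** This needs exactly 31 cures and a two-sided exact limit. Section 9.2 plans Poisson regression, Section 9.1 uses a one-sided alpha of 0.05, and the 70% bar is not set for this secondary analysis.
- **That confirmed reinfections ought to be counted as cleared and not excluded.** This is a matter of preference. With one such case, exclusion gives the lower figure (31/36 = 86.1% against 32/37 = 86.5%).

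**Conclusion.** The point holds for the further secondary analysis and no further. As worded, the rule would classify a strain that was present at entry and survived treatment as a new infection, and that analysis would drop a treatment failure. The first such case raises its cure estimate by about 2.3 to 2.5 points at n = 37 with 31 to 33 cures, and two cases raise it by about 4.8 to 5.1 points. The per-case gain is smaller if the whole stratum is the denominator.

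This rests on two assumptions: that exclusion means leaving the denominator, and that 0 to 2 such rebounds occur per stratum. With none, there is no bias. The primary SVR12 and the sample size stand as they are. It is a modest defect in a prespecified efficacy analysis, worth correcting before any rebound sequences are seen.

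**What to change.** In Sections 6.2 and 9.2, call a rebound a reinfection only if the rebound strain is absent from the participant's day 0 deep-sequence reads at a threshold set in advance. In the secondary analysis, count as treatment failure any rebound whose strain is found at day 0, and any rebound whose sequence is unresolved or failed. The threshold itself can go in the statistical analysis plan.

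The cost is about two sentences. Sequencing is already planned, and the comparison in Section 6.2 already needs a pre-treatment sequence; the change assumes that the day 0 sample can be read deeply enough to show minor strains. No visit, treatment or primary analysis changes.

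There are two downsides. The secondary cure rate may come out slightly less favourable, partly because unresolved cases count as failures. And a strain below the detection limit at day 0 would still be missed, so the problem is reduced and not removed.
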